## Rationale to compare Stereotactic Ablative Body Radiotherapy (SABR) to the current standard of care (SoC) therapies.

Thermal ablation is the preferred first line therapy for inoperable, solitary, early-stage HCC ≤ 3cm, however, there are two main limitations.

Firstly, the rate of contraindications to thermal ablation for patients with early-stage HCC can be high, and often underappreciated in real-world practice, as reported in several retrospective studies where 34-57% of patients did not undergo ablative therapies.(9, 10) Larger tumour size (>3cm) and certain anatomical locations (subphrenic, subcapsular, in close proximity to large vessels or central biliary structures) have been associated with higher local failure rates and increased complication rates. (12-14) Technical factors related to real-time image localisation or patient specific comorbidities may also come in to play. In a retrospective multicentre study of 245 patients with early-stage (BCLC 0/A) HCCs referred to multidisciplinary clinics within South Australia, 140 (57%) had contraindications to thermal ablation.(15) The main reasons cited were difficult/high risk tumour locations (66 patients) and tumour size >3 cm (65 lesions). A further Australian multicentre study of 253 BCLC early stage HCC patients in Victoria found 41.5% of patients underwent treatment stage migration to therapies such as TACE.(10) Treatment stage migration to non-curative therapies such as TACE is associated with lower local control rates at 2 years, in the order of 23 - 40%.(10, 16-18) A recent retrospective study of high dose TARE in early stage disease, however, reported very low rates (<10%) of local progression.(19) Given the retrospective nature of these studies there is likely significant bias limiting between treatment comparisons. SOCRATES will prospectively evaluate the propotion of non-surgical candidates with solitary HCC who undergo treatment stage migration. In this population of patients with HCC >3cm or HCC ≤ 3cm but ineligible for ablation **(Cohort 2)**, SOCRATES will evaluate the efficacy of modern transarterial therapy (inlcuding the option of combined TACE-ablation) compared to SABR in the first line setting within the context of a prospective randomised controlled trial.

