**Table 1: Summary of clinical studies reporting outcomes after SABR or PA in patients with early-stage HCC**

| **Study (Year)** | **Study Type** | **N** | **Study cohort/ Inclusion criteria** | **Intervention** | **Primary/ Secondary outcomes +/- significant predictors of LTC/ OS** |
| --- | --- | --- | --- | --- | --- |
| Dobrzycka et al. (2019) | Meta-analysis | 973 | 16 observational studies analysing SABR in early-stage HCC (single tumour ≤5cm or ≤3 lesions each ≤3cm, without macrovascular invasion or metastasis; CP A or B) | SABR | LTC: 94% (1-year); 92% (2-year) 93% (3-year)  OS: 90.9% (1-year); 67.5% (2-year); 73.4% (3-year)  Grade ≥3 toxicities: 5.3% |
| Rim et al. (2019) | Meta-analysis | 1950 | 32 observational studies analysing SABR in early to advanced stage HCC (with vascular invasion and/or extrahepatic metastasis) | SABR | Size <5cm: LTC: 91.0% (1-year); 86.3% (3-year)  Size <5cm: OS: 79.5% (1-year); 51.9% (3-year) |
| Park et al. (2020) | Retrospective review | 290 | Single centre, retrospective analysis of SABR in small HCC (<6 cm, ≤3 lesions, no vascular invasion or metastasis) | SABR | Size ≤3cm: LTC 93.3% (5-year)  Size >3cm: LTC 76.5% (5-year)  OS: 45% (5-year, whole cohort) |
| Liu et al. (2020) | Retrospective review | 96 | Single centre, retrospective analysis of SABR in early to advanced stage HCC | SABR | BCLC 0/A: FFLP: 94% (18 months)  BCLC 0/A: OS: 95% (12 months) |
| Mathew et al. (2020) | Prospective/ Retrospective review | 297 | Multicentre analysis of SABR in early-stage HCC without vascular invasion or metastasis, including large lesion >5cm (median size 2.7cm, range 0.5-18.1cm) | SABR | LTC: 93.4% (1-year); 86.7% (3-year)  Subgroup analysis- size <3cm: LTC 90% (3-year)  OS: 77% (1-year); 39% (3-year) |
| Yoon et al. (2020) | Phase II clinical trial | 50 | Single centre, single arm trial for early-stage HCC (single lesion ≤5cm, or ≤3 lesions with a sum of total diameter ≤5cm) | SABR | LTC: 100% (2-year); 97% (5-year)  OS: 96% (2-year); 78% (5-year) |
| Kubo et al. (2018) | Retrospective review | 65 | Single centre, retrospective analysis of SABR in BCLC 0/A HCC, <3 HCC, each >5cm | SABR | LTC: 100% (3- & 5-year)  OS: 56% (3-year) |
| ***Compared to RFA*** | | | | | |

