# TRIAL DESIGN

The study is designed as a phase II, prospective, randomised, parallel and open-label, multi-institutional superiority trial for patients with newly diagnosed early stage (BCLC 0/A) , solitary ≤8cm nodule HCC, ineligible for surgical resection or transplantation.

Patients with tumours ≤ 3cm **and** eligible percutaneous thermal ablation will be randomly assigned (1:1 ratio) to either thermal ablation or SABR.

Patients with tumours ≤ 3cm assessed as ineligible for thermal ablation or patients with tumours >3cm will be randomly assigned (1:1 ratio) to either SABR or standard of care which can include transarterial therapies (TACE or TARE) and or percutaneous thermal ablation (MWA or RFA). See **Figure 1: Study Schema.**

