### Cohort selection

Each participant will be allocated into a cohort based on the following criteria;

- Patients with HCC ≤ 3 cm deemed **eligible** for percutaneous thermal ablation by the local MDT^[[3]](#footnote-4)^ will be allocated to Cohort 1
- Patients with HCC >3cm or deemed **ineligible** for percutaneous thermal ablation by the local MDT will be allocated to Cohort 2

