### Randomisation Treatment Allocation

Participant will be randomised within each cohort;

- Participants in Cohort 1 will be randomly allocated (1:1) to receive either SABR verses percutaneous thermal ablation.
- Participants in Cohort 2 will be randomly allocated (1:1) to receive SABR verses SOC therapies
  *Note: SOC therapies include transarterial therapies (TACE or TARE) and/or MWA/RFA (alone or in combination).*

All randomisations will be completed through a web-based, password-protected randomisation system. Once the investigator has confirmed eligibility, the randomisation details are to be entered into the system by suitably delegated site personnel. The eligibility criteria will be reviewed by trial management staff prior to randomsiation. A confirmation of randomisation and treatment allocation will be emailed to site personnel, including the principal investigator.

Randomisation for both cohorts will be performed using block sizes of 4 to help ensure minimal imbalance in the size of treatment groups for each cohort.

Participants in each cohort will be stratified for;

1. Child-Pugh classification (A vs. B7)
2. BCLC stage (0 vs. A ; i.e. maximum tumour diameter ≤2 cm vs. >2cm)

Participants can only be randomised once in this trial.

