### Cohort 2 participants

- MWA or RFA may be used in cohort 2 for tumours >3cm if this represents standard of care therapy at the institution. It may be combined with transarterial therapies. All therapy is required to be completed within the primary therapy window of within 42 days from randomisation.
- MWA or RFA is not allowed for tumours ≤3cm in cohort 2 as this is a specific exclusion criteria for cohort 2. These patients are eligible for cohort 1.
- Technique will be as per local departmental protocols.

#### QA Measures for MWA or RFA in cohort 2

- Collection of treatment reports and mode of ablation (MWA v RFA, CT v USS-guided)
- Immediate post-ablation imaging and margin assessment will be as per departmental protocols and will not be assessed centrally for cohort 2.
  - Please see **APPENDIX 3: Imaging Guidelines** for recommendations on specific imaging sequences.

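### Cohort 2 joins two entry routes divided at 3 cm but stratifies size at 2 cm, so the mix of 2-3 cm and >3 cm tumours between arms is left to chance (minor, avoidable)

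*Protocol*

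**What the plan says.** **Entry to Cohort 2.** Section 3 (Trial Design): "Patients with tumours ≤ 3cm assessed as ineligible for thermal ablation or patients with tumours >3cm will be randomly assigned (1:1 ratio" to SABR or standard of care. Section 5.4.1 gives the same two routes. Eligibility extends to 8 cm.

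**Control treatment.** Section 6.1.2 divides at the same 3 cm line. Above it: "MWA or RFA may be used in cohort 2 for tumours >3cm if this represents standard of care therapy at the institution", with combination with transarterial therapy also allowed. At or below it: "MWA or RFA is not allowed for tumours ≤3cm in cohort 2 as this is a specific exclusion criteria for cohort 2".

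**Stratification.** Section 5.4.2 names two factors for each cohort: "Child-Pugh classification (A vs. B7") and "BCLC stage (0 vs. A ; i.e. maximum tumour diameter ≤2 cm vs. >2cm"). Section 14.2 confirms that there are two factors and refers back to 5.4.2. No section stratifies by 3 cm or by entry route.

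**Size and prognosis.** Section 1.3 associates tumours above 3 cm, and certain difficult locations, with more local failure. One single-centre SABR series in Table 1 reports 5-year local control of 93.3% at ≤3 cm; for the larger group it gives "Size >3cm: LTC 76.5% (5-year").

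**The concern.** A 2 cm cut suits Cohort 1, where every tumour is 3 cm or smaller. In Cohort 2 it separates only the ablation-ineligible tumours of 2 cm or less. The other stratum runs from just over 2 cm to 8 cm. It holds 2-3 cm tumours, for which the control arm may not use ablation, together with larger ones, for which it may.

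The size boundary that defines the cohort, and that decides whether ablation is permitted in the control arm, is therefore balanced only in part. The primary endpoint is local progression, and the protocol itself links size above 3 cm to local failure. In a cohort of 100, a sizeable difference between arms in the >3 cm share would make the result harder to read and the estimate somewhat less precise. Any breakdown by entry route would rest on groups whose balance had not been secured.

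**Working it through.** **1. The plan's own figure.** Section 14.1 assumes 65% versus 90%, two-sided alpha 0.05 and 80% power. With unpooled variance:

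n = (0.65×0.35 + 0.90×0.10) × (1.960 + 0.842)² / 0.25² = 0.3175 × 7.849 / 0.0625 = 39.87, so 40 per arm.

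40/0.80 = 50 per arm, N = 100. The stated size reproduces, and nothing below changes it.

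**2. What is left to chance.** Every patient at ≤2 cm in Cohort 2 entered by the ineligible route, so the 2 cm cut does balance that part. What is not controlled is the mix of 2-3 cm and >3 cm within the >2 cm stratum.

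**3. Assumptions (the size mix is not in the documents).**
- Share of Cohort 2 above 3 cm: 50%, 70% or 90%.
- Of the ≤3 cm patients, 30% or 50% are at ≤2 cm.
- Child-Pugh B7: 15%.

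The low end of the first range has one weak anchor, a retrospective series in section 1.3 on contraindications to ablation: "The main reasons cited were difficult/high risk tumour locations (66 patients) and tumour size >3 cm (65 lesions"). Those counts mix patients with lesions.

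**4. Approximate formula.** Let the >2 cm stratum hold n patients, of whom a fraction p are above 3 cm, split evenly between arms of 50. The SD of the arm difference in the >3 cm share is about

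(2/50) × √[ (n/4) × p(1−p) × n/(n−1) ].

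- 50% above 3 cm, 30% of the rest at ≤2 cm: n = 85, p = 50/85 = 0.588, SD ≈ 9.1 points.
- 70%: n = 91, p = 70/91 = 0.769, SD ≈ 8.1 points.
- 90%: n = 97, p = 90/97 = 0.928, SD ≈ 5.1 points.

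**5. Simulation** (stratified permuted blocks of 4, N = 100, 3,000 trials per row, current 2 cm cut):

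| >3 cm share | of ≤3 cm, share at ≤2 cm | SD (points) | P(≥10) | P(≥15) | P(≥20) |
|---|---|---|---|---|---|
| 50% | 30% | 9.2 | 30% | 9.7% | 3.6% |
| 50% | 50% | 8.3 | 25% | 6.9% | 2.2% |
| 70% | 30% | 8.1 | 24% | 6.3% | 1.5% |
| 70% | 50% | 7.2 | 19% | 3.3% | 0.6% |
| 90% | 30% | 5.5 | 7.6% | 0.9% | 0.1% |
| 90% | 50% | 4.9 | 4.4% | 0.2% | 0.0% |

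With a 3 cm cut the SD is about 2 points, and none of these thresholds was reached in any row. Section 5.4.2 gives blocks of 4 and section 14.2 gives 6 and 4; mixed blocks make little difference. Over further runs with mixed blocks and other ≤2 cm shares, P(≥10) is about 25-33%, 19-25% and 3-8% for the three mixes.

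**6. Effect on the endpoint.** Shift = imbalance × local-control gap by size.
- Gap of 16.8 points (93.3 − 76.5, the Table 1 series): 0.15 × 16.8 = 2.5 points.
- Gap of 10 points (75 − 65, the control assumptions for the two cohorts in section 14.1, as a rough proxy): 0.15 × 10 = 1.5 points.

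The planned difference is 25 points, and the shift can go in either direction.

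**The case against.** The strongest reply is that nothing here is an error. Allocation within Cohort 2 is random, entry route is balanced in expectation, and the test and confidence interval already allow for chance imbalance. Section 14.2 gives a reason for the factors chosen: disease severity and BCLC stage. All of that stands.

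A reader might infer three stronger things that the documents do not support.

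- *That the Cohort 2 comparison is confounded, or unbalanced by design.* It is neither. One factor is simply not forced into balance.
- *That entry route fixes the control therapy or the SABR dose.* Size decides only whether ablation is permitted. Transarterial therapy is open to both routes, and ablation above 3 cm depends on institutional practice. Table 3 sets SABR schedules by Child-Pugh class and dose-limiting organs, not by size or route.
- *That route is known to separate good from poor prognosis.* Section 1.3 names difficult location beside size as a risk for local failure, so both routes may be adverse. Section 1.4 says SABR controls larger tumours similarly well. The 16.8-point gap is a 5-year figure from one SABR series that admitted up to three lesions; the trial's endpoint is at 2 years in solitary tumours.

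An even mix is also uncertain. Every tumour from 3 to 8 cm goes to Cohort 2 even if it could be ablated, so the >3 cm share may be well above half, and the problem then shrinks. Covariate adjustment may be specified in an analysis plan not available here, so its absence from the protocol is no finding.

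What survives is narrow: the protocol fixes the cut, and for Cohort 2 a better one is available without extra strata or patients.

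**Conclusion.** The point holds as a minor, optional improvement. The mismatch between the 3 cm cohort boundary and the 2 cm stratum is plain in the text. Its consequence is an arm difference of 10 points or more in the >3 cm share in roughly 3-33% of trials, depending mainly on an unknown size mix, against about 0% with a 3 cm cut from the outset. The likely shift in the primary estimate is small: about 1.5-2.5 points for a 15-point imbalance, itself seen in at most about 13% of simulated trials. Validity, type I error and sample size are untouched. The figures rest on the assumed size mix, 15% Child-Pugh B7, and a local-control gap by size that is borrowed rather than known for this population.

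**What to change.** **If Cohort 2 accrual is still early:** for Cohort 2 only, replace the ≤2/>2 cm stratum with ≤3 cm (ablation-ineligible) versus >3 cm. Keep the 2 cm cut for Cohort 1. The number of strata and N do not change, and tumour size is already needed to assign the cohort.

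**If accrual is advanced:** leave the list unchanged and prespecify that the Cohort 2 comparison of freedom from local progression is stratified by, or adjusted for, size ≤3/>3 cm alongside Child-Pugh class. This uses a baseline variable already recorded.

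**Cost.** The first option needs a protocol amendment and a change of setting in the randomisation system. The ≤2 cm split is then no longer balanced in Cohort 2. A mid-trial change must be documented and removes only part of the imbalance: with half the patients already randomised and an even size mix, the SD falls only from 9.2 to about 9.2 × √0.5 = 6.5 points, and a difference of 10 points or more remains in about 11-18% of trials. The second option costs a sentence in the analysis plan.

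**To reconcile in the same amendment:** the note in section 5.4.2 lists ablation among Cohort 2 control therapies without a size limit, whereas section 6.1.2 sets one. The block sizes in sections 5.4.2 and 14.2 also differ.

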## Blinding

Participant and treating clinicians will not be blinded to the treatment assignment after the randomisation process. Given the distinct post-treatment imaging appearances of the different therapies it is also not feasible to reliably blind the local radiologists or central independent radiological review to treatment assignment.

Data collectors and analysers will be blinded to treatment assignment

# TREATMENT INTERVENTIONS

All primary therapy interventions are to commence within **28 days of randomisation** and must be completed within **42 days of randomisation**. This time window allows for additional percutaneous thermal ablation procedures (if initial ablation incomplete) or for combination therapy (eg. TACE-RFA for HCC >3cm) as part of the “first line” standard of care therapy.

## Percutaneous thermal ablation

### Cohort 1 Participants

- Technique (MWA or RFA) will be as per local departmental protocols and delivered as per local practice.
  - Patients undergoing irreversible electroporation or laparoscopic assisted ablations are not eligible for the study.
  - Relative contraindications for percutaneous thermal ablation include tumours <10mm from the gallbladder, hepatic flexure or stomach, or central bile ducts.
  - Hydro-dissection to protect adjacent structures, eg. bowel, is permitted.
- MWA or RFA will utilise CT, Cone-beam CT or ultrasound guidance aiming for an ablation margin of >5mm.
- A contrast-enhanced CT should be performed to verify ablation margins within 24 hours (refer to section 6.1.1.1 for further details).
- In the event of initial incomplete ablation, further attempts at complete ablation are recommended within the primary therapy timeframe. This will be considered part of the initial course of primary treatment.
- All primary therapy procedures including repeat ablations must be completed **within 42 days of randomisation**.

#### Quality Assurance (QA) measures for MWA/RFA in Cohort 1

- A post-ablation contrast enhanced CT is required to verify the ablation margin.
  This is recommended to occur within 24 hours post ablation and includes;
  - Immediate post-ablation contrast enhanced CT in the case of cone-beam CT or CT guidance
  - Contrast enhanced CT within 24 hours of US guided ablation^[[4]](#footnote-5)^

If there are concerns regarding adequacy of the margin repeat contrast enhanced CT or MRI imaging may be considered within 4 weeks of ablation.

- Central collection of initial baseline (pre-randomisation abdominal imaging scans as per **Table *5*: Schedule of Assessments**) and post-ablation imaging confirming complete ablation (and ablation margin), in DICOM format will be required.
  - Central review of the post-ablation contrast enhanced CT and ablation margin estimate will be conducted for each centre’s first case and sampling 1 in 5 thereafter. Additional sampling may be undertaken as determined by the central review team.
  - Submission of treatment details (including thermal ablation technique, estimation of minimum and maximum ablation margin) will also be required and should be collected via the SOCRATES Percutaneous Ablation Worksheet.
  - The post-ablation imaging data and treatment details for participants sampled for central review should be submitted to TROG within 2 weeks of the date of the ablation.
- Please refer to the SOCRATES HCC Quality Assurance (QA), Planning and Delivery Guidelines for further details.

### Cohort 2 participants

- MWA or RFA may be used in cohort 2 for tumours >3cm if this represents standard of care therapy at the institution. It may be combined with transarterial therapies. All therapy is required to be completed within the primary therapy window of within 42 days from randomisation.
- MWA or RFA is not allowed for tumours ≤3cm in cohort 2 as this is a specific exclusion criteria for cohort 2. These patients are eligible for cohort 1.
- Technique will be as per local departmental protocols.

#### QA Measures for MWA or RFA in cohort 2

- Collection of treatment reports and mode of ablation (MWA v RFA, CT v USS-guided)
- Immediate post-ablation imaging and margin assessment will be as per departmental protocols and will not be assessed centrally for cohort 2.
  - Please see **APPENDIX 3: Imaging Guidelines** for recommendations on specific imaging sequences.

## Transarterial therapy

Transarterial therapy this may include TACE or TARE as per local practice.

- TARE should aim to deliver a mean tumour dose of ≥120Gy.

### QA measures for TACE/TARE in cohort 2

- Collection of treatment reports.
- TACE
  - Document TACE technique eg cTACE, DEB TACE, B-TACE (conventional or bead)
  - Document chemotherapy agent/s used.
  - Document size of DEBs used.
- TARE
  - Document predicted mean dose to tumour on the basis of Tc-MAA scintigraphy and liver volume studies.
  - Document dosimetry method
    - BSA, partition, modified partition, voxel-based dosimetry.
  - Document software package/s used.
  - Document actual tumour dose achieved on basis of post-TARE PET-CT if possible.

## Stereotactic Ablative Body Radiotherapy (SABR)

Radiation therapy (RT) treatment details are provided in the SOCRATES HCC Quality Assurance (QA), RT Planning and Delivery Guidelines. The QA, RT Planning and Delivery Guidelines must be used as the primary source for planning and delivering radiotherapy treatment within the trial.

### Pre-trial Quality Assurance (QA) Program

All centres participating in this study must have completed pre-trial RT QA components **prior to enrolling patients** to the study.

- - - 1. Evidence of prior SABR Phantom Dosimetry Audit (conducted by an external independent auditing body)
      2. Completion of SABR Facility Questionnaire including Liver SABR Process and Motion Management Module
      3. Submission of benchmarking case if not previously performed for abdominal SABR technique*

**Additional credentialing activities may be required as deemed necessary by the Study team.*

Please refer to the SOCRATES HCC QA, Planning and Delivery Guidelines for further details on the RT QA program.

### RT Treatment Prescription and Schedule

SABR must commence within 28 days of randomisation and be completed within 42 days of randomisation. The local investigator has discretion over the prescription dose and fractionation schedule, within the following ranges stipulated. The fraction schedules permitted are as follows:

**Table 3: Recommended SABR Dosing Schedules**

| **CRITERIA** | **DOSE** | **FRACTIONS** | **BED_10_** |
| --- | --- | --- | --- |
| CP-A no dose limiting OAR* | 50 or  42-45 | 5  3 | 100  100-112 |
| CP-B7 no dose limiting OAR* | 40-50  36 | 5 (preferred)  3 | 72-100  79 |
| Dose limiting OAR* | 35-40 | 5 | 60-72 |

*Including meeting liver dose constraints.

The aim is to deliver the highest possible biological dose to the planning target volume (PTV ) from the protocol defined dose schedules, whilst adhering to the organ at risk (OAR) constraints. For participants with well compensated liver function (CP-A) and with tumours not abutting dose limiting organs, a schedule delivering ≥100 Gy BED10 is recommended. This corresponds to 42-45Gy in 3 fractions or 50Gy in 5 fractions delivered to ≥95% of the PTV.

Treatment fractions are recommended to be delivered on 2-3 non-consecutive days per week, over a period of ≤ 15 days. Delays and treatment gaps should be avoided, however if gaps occur, please refer to the SOCRATES HCC QA, RT Planning and Delivery Guidelines for further information.

